## Abstract

**Background:**

Although opioids are commonly prescribed in clinical anaesthesia, the significant side effects attributed to their overuse are raising increasing concerns. One way to reduce perioperative opioid consumption is to apply opioid-reduced anaesthesia (ORA) and even opioid-free anaesthesia (OFA), which involves regional techniques, neuraxial anaesthesia, nonopioid analgesics or combined use. The aim of this study was to investigate whether the application of OFA by using esketamine in intraoperative analgesia could minimize the side effects of postoperative nausea and vomiting (PONV), as well as other short-term side effects related to anaesthesia.

**Methods/design:**

The study was designed as a prospective, randomized, controlled, multicentre trial. A total of 278 patients were enrolled; participants were nonsmoking female patients aged 18–50 years and scheduled for laparoscopic appendectomy or cholecystectomy, ASA at I–III, with no serious physical or mental diseases. Both groups received usual perioperative care except for the analgesic medication of either esketamine or sufentanil. The primary outcome was the incidence of PONV 3 days after surgery. Secondary outcomes included recovery status, pain, sedation level and overall recovery, delirium and cognition, anxiety and depression and total consumption of analgesic agents.

**Discussion:**

This trial may show that the synergy of esketamine and propofol anaesthesia reduces PONV as well as other short-term adverse events, thereby providing a better safety and satisfaction profile of ERAS for laparoscopic appendectomy and cholecystectomy.

**Trial registration:**

Chinese Clinical Trial Registry ChiCTR2100047169. Registered on June 9, 2021

## Introduction

Opioids are commonly prescribed in the peri-operative period for analgesia and pain management. However, immediate adverse reactions or the long-term sequelae of chronic effects attributed to the overuse of opioids perioperatively may lead to significant morbidity and mortality [1]. It seems that the incidence of opioid-related adverse events is generally underestimated in the clinic, as previous research has reported that opioid-related adverse events may occur in 12% of surgeries [2]. One common side effect of opioids is postoperative nausea and vomiting (PONV), which contributes to a delay in oral intake and mobilization with a prolonged hospital length of stay or unexpected hospital readmissions [3]. Other side effects including pruritis, respiratory depression, and constipation could also lead to prolonged hospital admissions. In addition, recent evidence also reveals the potential role of opioids in cancer recurrence [4, 5]. Despite all these severe adverse events, the intraoperative use of opioids remains a central part of anaesthesia practice.

As doubts have increased, more attention has been given to reducing perioperative opioid consumption. The recently developed enhanced recovery after surgery (ERAS) protocols have promoted several opioid alternatives, including neuraxial anaesthesia, peripheral nerve blocks and nonopioid adjuncts. Opioid-free anaesthesia (OFA) is an opioid-sparing technique, which focuses on multimodal or balanced analgesia [6, 7]. Generally, the implementation of opioid-reduced anaesthesia (ORA) or OFA often involves regional techniques, neuraxial anaesthesia, nonopioid analgesics or their combined use. Among them, nonopioid medications have received wide attention, including acetaminophen, nonsteroidal anti-inflammatory drugs, alpha-2 agonists, *N*-methyl-d-aspartate (NMDA) receptor antagonists, gabapentioids and antidepressants [8, 9]. Substantial evidence has suggested that using OFA with nonopioid adjuncts not only minimizes the adverse effects of opioids but also enables earlier ambulation and return of bowel function and ultimately facilitates enhanced recovery after surgery (ERAS) protocols [10, 11].

Esketamine, a right-handed split of ketamine, might be a potential substitute for opioids in ORA or OFA. Esketamine is a noncompetitive *N*-methyl-d-aspartate (NMDA)-receptor antagonist, and its anaesthetic effect is approximately twofold higher than that of racemic ketamine, with a lower incidence of psychotropic side effects at equivalent doses [12, 13]. In addition, due to a ketamine-induced increase in sympathetic tone, esketamine results in less respiratory depression and hypotension than other anaesthetics and analgesics [14]. Studies also report that esketamine creates less impairment in concentration capacity and primary memory and fewer cardiopulmonary adverse effects and may lead to a faster recovery [15, 16]. Furthermore, one recent study suggested that esketamine could be an attractive additive to propofol sedation instead of opioids, as an adequate level of sedation and analgesia could be achieved with less propofol [17].

## Methods/design

### Aim of the study

We hypothesize that the application of OFA by using esketamine in intraoperative analgesia may minimize the side effects of postoperative nausea and vomiting (PONV), as well as other short-term side effects related to anaesthesia, while maintaining the same satisfaction level of patients. To test this hypothesis, we compared the two groups that underwent laparoscopic appendectomy and cholecystectomy: group E received propofol/esketamine sedation, and group F received propofol/sufentanil sedation. Both groups received standard deep sedation with propofol target-controlled infusion (TCI) provided by specialized sedation anaesthesia nurses. The primary objective of this study is to test the hypothesis that esketamine-based opioid-free anaesthesia alleviates postoperative nausea and vomiting in patients who underwent laparoscopic surgery.

### Study settings

The study is designed as a prospective, randomized, controlled, multicentre trial. The protocol is in accordance with the Standard Protocol Items: Recommendations for Interventional Trials (SPIRIT) statement [18]. This trial is registered at ClinicalTrial.gov with ID number ChiCTR2100047169. The sponsor of this trial is the Department of Anaesthesiology of the Shidong Hospital, University of Shanghai for Science and Technology. The sponsor is responsible for the collection, management, analysis and interpretation of the data as well as the writing of the report and the decision to submit the report for publication. The study is supported by the Yangpu District Good-Doctor Program.

The participating clinical centres are as follows: (1) Department of Anaesthesiology, Shidong Hospital of Shanghai, University of Shanghai for Science and Technology; (2) Department of Anaesthesiology, Eastern Hepatobiliary Surgery Hospital, Second Military Medical University; (3) Department of Anaesthesiology, Shuguang Hospital, Shanghai University of Traditional Chinese Medicine; and (4) Department of Anaesthesiology, Shanghai East Hospital, Tongji University School of Medicine.

### Inclusion and exclusion criteria

The inclusion criteria were as follows: (1) nonsmoking female patients who were 18–50 years old with a planned laparoscopic appendectomy or cholecystectomy from October 1, 2021, to October 1, 2022; (2) American Society of Anaesthesiologists (ASA) classification I–III; (3) no analgesic/sedative medication was used within 24 h before surgery; (4) no serious endocrine, cardiovascular and respiratory diseases before surgery; (5) no mental abnormality; and (6) provision of signed informed consent.

The exclusion criteria included patients who (1) had an allergic history of anaesthetic drugs or contraindications of esketamine, nonsteroidal anti-inflammatory drugs or dexmedetomidine; (2) had mental disorders, preoperatively screened using a neuropsychiatric inventory; (3) had poorly controlled or untreated hypertension with resting arterial pressure over 180/100 mmHg; (3) had addiction or dependence on opioid or hypnotic drugs; and (4) had respiratory infection or asthma before surgery.

Patients who were enrolled but met one of the following criteria were excluded from the study: (1) incomplete case report form or lost to follow-up and failed to make an effective and safety assessment, (2) change of anaesthesia method due to unexpected incident or surgery requirement during the surgery, (3) operation could not be continued due to unexpected incident during the surgery and (4) other diseases post-surgery required urgent treatment.

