### Dropout criteria

The dropout criteria are as follows: (1) withdrawal of consent by the participants or their legal representative and (2) loss to follow-up.

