### Ethics issues

This study was approved by the Ethics Committee of Shidong Hospital, University of Shanghai for Science and Technology (Ethics number: YPSDKY2021-02-009). Designated doctors explained this trial to interested potential participants in detail and provided them with the informed consent form. Participants were given at least 6 h to decide whether they wished to participate in the trial. The informed consent form was signed by the participant or his or her trustee or guardian, and consent could be withdrawn at any time during the trial. Written informed consent and the patient’s baseline data were obtained before randomization. Moreover, participants were encouraged to contact the research team if they had any health concerns during the trial.

The schedule of enrolment, intervention and assessment is reported according to the SPIRIT statement (Fig. 1).

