### Statistical analysis

Statistical analyses will be performed using SPSS 25.0 (IBM SPSS Statistics, Armonk, NY). An intention-to-treat (ITT) approach will be used to analyse the data. All data will be checked for normal distribution using the Kolmogorov test. For normally distributed data, continuous variables will be analysed using the independent Student’s *t* test, and the variables will be presented as the mean ± standard deviation (SD). Nonnormally distributed data will be compared using the Mann‒Whitney *U* test where appropriate, and data will be presented as the median and interquartile range (IQR). For categorical variables, cross-tabulation and the Pearson chi-squared test will be applied, and variables will be categorized as numbers and/or percentages of the total. A logistic regression model will be applied to detect any potential confounding factors. To compare the continuous measurements of HR and NIBP between the groups, the area under the curve (AUC) for each value will be calculated over the different measurement time points during the procedure. To compare the continuous measurements of HR and NIBP between the groups, the area under the curve (AUC) for each value will be calculated over the different measurement time points during the procedure. Missing data are neglected or multiple imputation will be used when > 40% and identified as missing, not at random. A *p* value < 0.05 with two tails will be considered statistically significant.

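### Four exclusion rules that operate after randomisation conflict with the stated intention-to-treat analysis, so the PONV denominator is undefined and the comparison may be biased in either direction

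*Protocol article*

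**What the plan says.** The section Inclusion and exclusion criteria ends with a list headed "Patients who were enrolled but met one of the following criteria were excluded from the study". It has four rules, numbered here as in the article:

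- Rule 1 concerns patients who cannot be assessed: "incomplete case report form or lost to follow-up and failed to make an effective and safety assessment".
- Rule 2 concerns a switch of anaesthetic technique, and its wording is "change of anaesthesia method due to unexpected incident or surgery requirement during the surgery".
- Rule 3 concerns surgery that had to be abandoned because of an incident in theatre.
- Rule 4 concerns later illness, and its wording is "other diseases post-surgery required urgent treatment".

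The next section, Dropout criteria, gives two grounds: "withdrawal of consent by the participants or their legal representative and (2) loss to follow-up". Loss to follow-up therefore appears in both lists.

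The Statistical analysis section says: "An intention-to-treat (ITT) approach will be used to analyse the data". It also says that missing data are neglected, or multiply imputed above 40% missing when judged not at random.

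On timing, the Ethics issues section says: "Written informed consent and the patient’s baseline data were obtained before randomization". The caption of Fig. 1 places allocation at t0 and the pre-anaesthesia time point at t1.

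**The concern.** An analysis that drops randomised patients because of events during surgery or follow-up is not intention-to-treat. The article fixes two incompatible populations for the primary outcome and does not say which one prevails. An analysis plan could not honour both.

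The validity of the PONV comparison is at stake. Rules 2 to 4 can follow from the allocated drug. The Introduction and Discussion expect the arms to differ in respiratory depression and circulatory stability, and the safety section names respiratory depression and cardiocirculatory instability as adverse events. An incident of that kind could lead to a changed anaesthetic, a stopped operation or urgent treatment. If such removals differ between arms in number or in PONV risk, randomisation no longer protects the comparison. The same removals could take patients who needed urgent treatment out of the between-arm safety comparison.

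**Working it through.** **Do the rules act after randomisation?** Consent and baseline data precede randomisation, and allocation (t0) precedes anaesthesia (t1). Rules 2 and 3 describe events during surgery, rule 4 an event after surgery, and rule 1 a failure of follow-up or assessment. Even if enrolment is taken to begin before randomisation, each event falls after allocation.

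**Does any text reconcile the two statements?** No section assigns the rules to a per-protocol set, and none says that excluded patients stay in the efficacy or safety comparison. Rule 1 also removes patients whom the missing-data statement would otherwise have to handle.

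**The plan's own sample size.** Inputs from Sample size calculation and Statistical analysis: 37.3% versus 20%, two-sided alpha 0.05, power 90%, 1:1 allocation. With unpooled variance:

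n = (1.960 + 1.282)² × (0.373 × 0.627 + 0.20 × 0.80) / (0.373 − 0.20)² = 138.3, rounded up to 139 per group.

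This matches the stated figure. The pooled-variance formula gives 142, and power at 139 per group is then 89.5%. The 278 patients in the abstract are exactly 2 × 139, so no allowance for removals is visible. If 10% were removed from each arm, about 125 per arm would remain and power would be about 86.1%.

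**How large could the bias be?** The article gives no exclusion frequency and no PONV rate among excluded patients, so all of the following rests on assumptions: 37.3% PONV in both arms (no true effect), and removals from group E only. Let x be the fraction removed and q the PONV rate among those removed.

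- Remaining rate in group E: (0.373 − x·q)/(1 − x), in 139(1 − x) patients.
- Spurious difference: d = 0.373 minus that rate.
- Chance of a two-sided p < 0.05: Φ[(d − 1.96·SE0)/SE1] + Φ[(−d − 1.96·SE0)/SE1], with SE0 the pooled and SE1 the unpooled standard error.

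For x = 0.10:

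- q = 0.6: (0.373 − 0.060)/0.9 = 0.348, d = 0.025, rejection probability 0.071.
- q = 1.0: (0.373 − 0.100)/0.9 = 0.303, d = 0.070, rejection probability 0.221.

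Each cell below gives the remaining group E rate, then the type I error:

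| Removed from group E | q = 37.3% | q = 60% | q = 80% | q = 100% |
|---|---|---|---|---|
| 5% | 37.3%; 5.0% | 36.1%; 5.5% | 35.1%; 6.7% | 34.0%; 8.7% |
| 10% | 37.3%; 5.0% | 34.8%; 7.1% | 32.6%; about 13% | 30.3%; 22.1% |
| 15% | 37.3%; 5.0% | 33.3%; 10.2% | 29.8%; about 24% | 26.2%; 47.3% |

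The direction is not fixed. If the 10% removed from group E all lacked PONV, the remaining rate would be 0.373/0.9 = 41.4%, which counts against esketamine. Removing patients with PONV from group F instead would also reverse the direction.

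**The case against.** The strongest defence is that this is a condensed article. Rules 2 to 4 sit beside the dropout criteria and could be read as withdrawal rules, with the intention-to-treat statement governing the analysis. That reading is possible, but the text removes patients from the study without qualification, and rule 1, with its reference to an incomplete case report form, reads as an analysis rule. The conflict therefore stands.

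Several other points limit what can be concluded, and they stand:

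- **Rule 1.** A reader might infer that it discards assessable patients. With its closing qualifier it covers patients with no efficacy and safety assessment, so it is a missing-outcome problem.
- **Post-hoc selection.** A reader might call the resulting set post-hoc. The rules are written into the protocol, so the set is prespecified, although it is defined by post-randomisation events.
- **Safety data.** A reader might infer that serious events vanish from the safety data. The safety section says that all adverse events were documented and discussed by the monitoring committee, and rule 4 speaks of other diseases. It is unclear only whether excluded patients' events enter the comparison between arms.
- **Drug-related causes.** Rule 2 also covers requirements of the surgery. The Intervention section provides for repeat blinded doses in the allocated arm, so inadequate analgesia is a weak trigger, and so is a psychotomimetic reaction in an intubated patient kept at BIS 40–60. Haemodynamic instability is the plausible route.
- **Blinding.** Blinded anaesthesiologists and patients limit deliberate selective removal. Blinding does not stop removals caused by a drug's own effects.

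**Conclusion.** The contradiction is in the text and needs no assumption: the exclusion rules and the intention-to-treat statement define different populations for the primary outcome. Because this sets the PONV denominator, it must be settled before analysis.

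Bias is possible but not shown. With 10% lost from one arm only and no true effect, type I error ranges from 5% (removed patients have the average PONV rate) through about 7% (60% of them have PONV) to about 22% (all do). The exclusion frequency, the one-arm loss and the PONV rate among those removed are all assumptions. A reader might take the 22% as a forecast, or as a bias in favour of esketamine. The article supports neither, since the effect is nil or reversed under assumptions that are equally open. Loss of patients from the safety comparison is likewise a possibility that the wording leaves open.

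**What to change.** Reconcile Inclusion and exclusion criteria, Dropout criteria and Statistical analysis as follows.

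- **Primary analysis:** all randomised patients by allocated arm, with PONV counted to 72 h whether or not the anaesthetic was changed, the operation was abandoned or urgent treatment was needed.
- **Rule 1 and dropouts:** treat as missing outcome data, with a sensitivity analysis over a range of assumptions for the missing PONV results. The current missing-data statement alone would not be enough, because neglecting missing data drops the same patients again.
- **Safety:** compare the arms in all patients who received any study drug.
- **Rules 2 to 4:** keep them only to define a labelled per-protocol sensitivity set, with exclusions tabulated by arm and reason.

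The cost is wording, plus completion of the 72 h follow-up that the schedule already contains. No extra enrolment is needed, and the target of 139 per group is unchanged. There are two downsides. The effect is somewhat diluted if anaesthetic changes are frequent. Also, recruitment began on October 1, 2021, so 72 h data may be unrecoverable for patients already excluded and not followed. Those patients should be reported by arm and handled as missing.

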### Dropout criteria

The dropout criteria are as follows: (1) withdrawal of consent by the participants or their legal representative and (2) loss to follow-up.

### Ethics issues

This study was approved by the Ethics Committee of Shidong Hospital, University of Shanghai for Science and Technology (Ethics number: YPSDKY2021-02-009). Designated doctors explained this trial to interested potential participants in detail and provided them with the informed consent form. Participants were given at least 6 h to decide whether they wished to participate in the trial. The informed consent form was signed by the participant or his or her trustee or guardian, and consent could be withdrawn at any time during the trial. Written informed consent and the patient’s baseline data were obtained before randomization. Moreover, participants were encouraged to contact the research team if they had any health concerns during the trial.

The schedule of enrolment, intervention and assessment is reported according to the SPIRIT statement (Fig. 1).

**Fig. 1 Fig1:**
[figure not shown]
Schedule of enrolment, intervention and assessment according to the Standard Protocol Items: Recommendations for Interventional Trials (SPIRIT) statement. Time points for implement of the study: *t*_−1_: when enrolled, *t*_0_: allocation, *t*_1_: before anaesthesia, *t*_2_: TCI propofol reached equilibrium, *t*_3_: in 3 min after sufentanil or esketamine infusion, *t*_4_: immediately after intubation, *t*_5_: in 5 min after intubation, *t*_6_: pneumoperitoneum, *t*_7−*x*_ in each 15 min till the end of the surgery; *t*_*a*−*g*_ refers to 0, 2, 4, 8, 24, 48 and 72 h after anaesthesia

### Sequence generation and allocation concealment

Blocked randomization was conducted. A randomization sequence was generated using a computerized random number generator, and patients who met the enrolment criteria were randomized in a 1:1 ratio to either the control or esketamine anaesthesia group. Once the patient was qualified for the study, the project coordinator opened a sealed opaque envelope with random serial numbers. Only the statistician and the project coordinator knew the treatment allocation of each participant.

### Blinding

The study was performed as a double-blinded study. The esketamine (1 mg/kg) or sufentanil (0.5 μg/kg) used for induction of anaesthesia was diluted to 20 ml solution with normal saline, and another same dosage was also diluted to 20 ml solution, preparing for use during surgery if necessary. The drugs of the two groups were prepared by the nurse, who subsequently withdrew from the study and did not participate in anaesthesia management, postoperative follow-up and other affairs. Therefore, the anaesthesiologists were blinded to the grouping. All patients were blinded as well.

### Intervention

All patients fasted at least 6 h before surgery. Peripheral venous access was opened after entering the operating room, and antibiotic prophylaxis was given according to hospital standards. Measurements of heart rate (HR), electrocardiogram (ECG), noninvasive blood pressure (NIBP), respiratory rate (RR), oxygen saturation (SpO_2_), end-tidal carbon dioxide (etCO_2_), sedation level measured by BIS and nociception level by Surgical Pleth Index (SPI) were recorded.

Procedural sedation was performed by experienced anaesthesiologists. Both groups were sedated by a propofol TCI system (Propofol 1% MCT Fresenius). We started propofol TCI in both groups with a targeted plasma level of 2–4 μg/ml. Upon reaching this plasma level, 0.1–0.2 mg/kg cisatracurium besilate was administered. Group E was treated with 1 mg/kg esketamine (Ketanest S, Pfizer), and the infusion lasted for 30 s. Group F was treated with 0.5 μg/kg sufentanil (Rapifen, Janssen-Cilag), with infusion lasting for 30 s. The esketamine (1 mg/kg) or sufentanil (0.5 μg/kg) used for induction of anaesthesia was diluted to 20 ml solution with normal saline, and another same dosage was also diluted to 20 ml, preparing for use during surgery if necessary. One of three of the induction dosage (6.5 ml solution) was given each time if necessary. Under special circumstances, the nurse who had prepared the medicines provided the corresponding medicines again. Mechanical ventilation was applied followed by tracheal intubation; BIS was maintained at 40–60, ETCO_2_ was maintained at 35–45 mmHg and muscle relaxant was given as needed.

All anaesthetics were stopped when pneumoperitoneum stopped; then, muscle relaxant antagonists were applied according to their conditions, and endotracheal intubation was removed according to the anaesthesiologist’s judgement. “Ready for discharge” was declared when a Steward recovery score was ≥ 9. Parecoxib or flurbiprofen was applied intravenously when postoperative analgesia was necessary, and if parecoxib or flurbiprofen did not work well, peripheral nerve blocking was given as needed. Postoperative antiemetic drugs of dexamethasone, metoclopramide or 5-hydroxytryptamine antagonists for PONV were also applied accordingly as needed. 5-Hydroxytryptamine antagonists (4 mg ondansetron) for PONV were administered intravenously.

